#### Measures of adherence

Data will be collected on the number of intervention visits attended. Attendance at treatment sessions is anticipated to decline over time, but, in keeping with prior studies in the weight control literature, those who attend more sessions are expected to have better weight loss outcomes [59, 60]. Adherence to self-monitoring, a known predictor of treatment success [61, 62], will be assessed by tracking the total number of self-monitoring diaries that are completed and turned into the group leader during the interventions.

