#### Treatment components common to both conditions

##### Treatment length

In both conditions, the 6-month treatment program will be delivered in interactive weekly group sessions (check-in period, didactic information, and group discussion) lasting approximately one hour. This meeting schedule is consistent with best practices according to recent AHA/ACC/TOS guidelines [9].

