##### Diet

Participants will be placed on a standard caloric and fat restricted diet (e.g., 1200–1800 kcals/day, ≤30% fat) consistent with published trials [33, 35, 38] and recent AHA/ACC/TOS guidelines [9]. They will receive sample meal plans, a fat and calorie guidebook and internet references, and paper copies of a daily self-monitoring diary for diet and physical activity. Participants will be allowed to record their diet in the paper diaries or use an online tracking app or program of their choice (e.g., MyFitnessPal). Interventionists will provide weekly written feedback on dietary choices.

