##### Exercise

Participants will be encouraged to gradually increase their physical activity until they are engaging in 50 min of moderate intensity activity on 5 days per week (100 min/wks 1–4; 150 min/wks 5–8; 200 min/wks 9–16; 250 min/wks 17+) [9]. Brisk walking and accumulating activity through multiple short bouts will be encouraged [39], and participants will be instructed to monitor their daily exercise minutes in the self-monitoring diary or using an online tracking app or program of their choice [40].

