#### Treatment components specific to the SDT condition

The primary difference between conditions is that dyads in SDT-WL will receive additional training in how to provide needs support for each other’s weight loss efforts. Adapting effective strategies from the literature on needs supportive behaviors in educators, coaches, and healthcare providers [27–29, 32, 42–45], spouses will be encouraged to: 1) elicit and acknowledge the other’s perspectives, 2) minimize efforts to control, 3) use non-judgmental, non-critical language, 4) support each other’s initiatives for change, and 5) develop empathic responding as a substitute for evaluative praise or condemnation. This type of support is distinct from more directive forms of support, such as reminding a spouse of his/her goal or encouraging certain types of eating [21]. Couples will be taught basic concepts of needs support using an “ABC” model (Table 1) and will be provided opportunities to practice these new behaviors in group meetings and receive feedback from interventionists. Spouses will be encouraged to incorporate these behaviors into their relationship between sessions and to monitor targeted support behaviors in an ongoing fashion. A variety of clinical tools will be used to facilitate adoption of these behaviors including: 1) handouts of key points in the ABC model, 2) cartoon vignette dialogues similar to those used in Faber and Mazlish’s *How To Talk To Kids So Kids Will Listen and Listen So Kids Will Talk* [46] depicting unhelpful communication patterns and more effective ways of communicating, 3) role-plays (facilitated by the interventionists) to provide couples the opportunity to practice needs supportive behaviors and receive personalized feedback from interventionists, 4) group discussions of all the concepts, vignettes and other material relevant to autonomy supportive behavior, and 5) weekly written reflection on support provided and received from one’s spouse with examples shared at group sessions.

**Table 1 Tab1:** “ABCs” of Needs Support Training Objectives

Basic Concept	Training Goal	Example exercises
**A**sk to avoid assumptions	• Teach spouses to ask what would be most helpful • Teach spouses to discuss behaviors that promote weight loss and behaviors that sabotage weight loss.	• Have spouses discuss what would be most helpful; discuss what gets in the way of providing this support.

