##### Assessments

Assessments (Table 2) will be conducted at baseline, 3, 6, and 12 months by research assistants blinded to group assignment.

**Table 2 Tab2:** Data Collection Schedule for TEAMS

		Month			
Construct	Specific Measures	0	3	6	12
Demographics	Age, gender, race, ethnicity, education, income, work status, household structure, weight history, weight status of household members	x			
Anthropometrics and Behaviors	Weight and height	x	x	x	x
	Block Dietary Fat Screener	x		x	x
	Block Fruit/Vegetable/Fiber Screener	x		x	x
	Paffenbarger Activity Questionnaire	x		x	x
	Weight Control Strategies Questionnaire	x		x	x
	Self-Weighing Frequency	x	x	x	x
	Self-Report Habit Index - Automaticity	x	x	x	x
	Grocery Shopping, Meal Preparation, Shared Meal Patterns	x		x	x
	Perceived Similarity of Dyadic Eating/Exercise Habits	x		x	x
SDT Model	Important Other Climate Questionnaire	x	x	x	x
	Videotaped Conversation Coded for Types of Support	x		x	x
	Autonomous Self-Regulation-Weight Management	x	x	x	x
	Perceived Competence for Weight Management	x	x	x	x
Social Support and Relationship	Sallis Social Support Questionnaire for Eating and Exercise	x	x	x	x
	Directive support from Spouse	x	x	x	x
	Quality of Marriage Index	x	x	x	x
	Revised Dyadic Adjustment Scale (Cohesion subscale)	x	x	x	x
	Health-Related Social Control from Spouse	x	x	x	x
Process Measures	Attendance at groups		x	x	x
	Adherence to self-monitoring (completion of diaries)		x	x	x
	Health Care Climate Questionnaire			x	
	Satisfaction with program			x	

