#### Statistical analyses to support the secondary aims

The same dyadic data analysis procedure as noted above will be employed to examine weight loss maintenance from 6 to 12 months, treatment adherence, and treatment satisfaction between groups. This strategy will also be used to explore the effect of needs support on weight change from baseline to 6 and 12 months, controlling for the effects of other, more directive forms of support. Finally, mediation analysis will explore SDT variables (i.e., autonomous self-regulation and competence for healthy behavior) as mediators of the effect of perceived needs support on weight outcomes.

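### Self-monitoring adherence is counted as diaries handed in, but both arms may log in an app instead and no rule counts app records

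*Protocol article*

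**What the plan says.** Measures of adherence defines self-monitoring adherence by "tracking the total number of self-monitoring diaries that are completed and turned into the group leader during the interventions". The matching row of Table 2 (Assessments) begins "Adherence to self-monitoring (completion of diaries" and names no other type of record.

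The diary is introduced under Diet, where participants are given "paper copies of a daily self-monitoring diary for diet and physical activity". The same section then says: "Participants will be allowed to record their diet in the paper diaries or use an online tracking app or program of their choice". Under Exercise, participants are told to "monitor their daily exercise minutes in the self-monitoring diary or using an online tracking app or program of their choice". Both sections sit under the heading "Treatment components common to both conditions", so the choice is open to SDT-WL and BWL alike.

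Statistical analyses to support the secondary aims compares "weight loss maintenance from 6 to 12 months, treatment adherence, and treatment satisfaction between groups", and Study aims also lists adherence among the secondary aims. It is therefore a named between-arm outcome and not only a process log.

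**The concern.** What is counted does not match what participants may do. The Exercise section sets the diary and the app against each other as alternatives, and the adherence count then uses the diary term alone. Followed to the letter, someone who logs every day in an app adds nothing to the count, while an occasional diary user adds something. The measure then reflects choice of recording medium as well as self-monitoring.

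At stake is one component of one secondary outcome. The article itself treats self-monitoring as an established predictor of treatment success, so a distorted count also weakens any later use of it to explain weight results.

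**Working it through.** **1. Could another part of the article repair the rule?** Two places come close.
- Diet says interventionists give written feedback each week on dietary choices. This suggests leaders see some record from app users. It gives no route for app logs, does not mention exercise records and is not tied to the adherence count.
- Weight-related strategies and habits adds questions on use of apps and websites to a scale that looks back over 6 months. Table 2 schedules that scale at 0, 6 and 12 months. It can show who used apps, but it cannot rebuild adherence week by week.

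So no stated rule brings app records into the count.

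**2. Inputs for an illustration.** The article gives no figure for self-monitoring adherence or app use, so there is nothing to reproduce. Everything below is assumed except the weekly sessions over 6 months, taken as about 26 weeks.
- m = true proportion of weeks self-monitored in an arm, taken as the same for app and diary users
- a = share of the arm using an app
- worst case: app records are never counted

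Observed adherence = m(1 − a). Observed difference = m₁(1 − a₁) − m₀(1 − a₀), SDT-WL minus BWL.

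**3. Results in percentage points.**

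| App share, SDT-WL / BWL | True 75% v 60% | True 60% v 60% |
|---|---|---|
| 0 / 0 | 15.0 | 0 |
| 30 / 30 | 10.5 | 0 |
| 50 / 50 | 7.5 | 0 |
| 30 / 40 | 16.5 | +6 |
| 40 / 30 | 3.0 | −6 |
| 30 / 50 | 22.5 | +12 |
| 50 / 30 | −4.5 | −12 |

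Examples: 0.75 × 0.70 − 0.60 × 0.70 = 0.105; 0.60 × 0.60 − 0.60 × 0.70 = −0.06. Equal uptake creates no false difference but shrinks a true one. Unequal uptake moves the result in either direction.

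**4. Loss of precision under equal uptake.** Zeros from app users also add variance. Assume 26 weekly diaries, means of 19.5 and 15.6 (75% and 60% of 26) and an SD of 7 among those whose records are counted. The variance in an arm with mean M is (1 − a) × 7² + a(1 − a) × M².

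| App share, both arms | Difference, diaries | SD | Standardised effect |
|---|---|---|---|
| 0 | 3.90 | 7.00 | 0.56 |
| 20% | 3.12 | 9.44 | 0.33 |
| 30% | 2.73 | 9.99 | 0.27 |
| 50% | 1.95 | 10.12 | 0.19 |

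**5. If leaders count some app records.** With a fraction c of app records accepted, replace a by a(1 − c). At a = 0.30 in both arms and c = 0.5, the true 15 points become 15 × (1 − 0.15) = 12.75. At c = 1 the problem disappears.

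**The case against.** The strongest reply is that the definition does not contain the word paper, and that no section says app records are refused or scored as zero. A reader might infer that app users are classed as non-adherent; the article does not say so. Weekly dietary feedback covers all participants, so leaders probably see something from app users and may accept a printout as a diary. The detail could sit in the full protocol or the intervention manuals.

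Part of this stands. The zero score is the literal consequence of the wording, not a stated rule, and practice may be better than the text. But the article does not merely leave out a detail. It states a scoring rule in one unit, the diary handed in, having offered an alternative to that unit. Without a written rule, leaders may also differ in what they accept.

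A second reply is that the option is the same in both randomised arms, so the comparison is fair. This holds against any claim of demonstrated bias: with equal uptake and no true difference, the observed difference is zero. It does not answer attenuation or lost precision. Nor does randomisation guarantee equal uptake, because the medium is chosen afterwards. SDT-WL alone has a "weekly written reflection on support provided and received from" one's spouse, which might favour written records, while its stress on personal choice might favour apps. The article supports neither direction.

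**Conclusion.** The definition of self-monitoring adherence does not fit the self-monitoring methods the trial permits. On its literal reading it under-counts app users, lowers measured adherence and attenuates a true arm difference. With app records never counted, a 15-point gap becomes 10.5 points at 30% uptake in both arms and 7.5 at 50%. These figures rest on assumed adherence, assumed uptake and no acceptance of app logs; they show the mechanism and do not estimate its size in this trial.

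A reader might go further and conclude that the between-arm adherence comparison is wrong. The documents do not support that: a false difference requires uptake to differ by arm, and nothing in the article shows that it will. The weight outcome and session attendance do not depend on recording medium.

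Table 2 also marks attendance and diary completion at month 12, after the 6-month programme has ended. This is a clerical matter, since Measures of adherence already confines the diary count to the intervention period.

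**What to change.** Define self-monitoring adherence as the number of treatment weeks (or days) with a diet and exercise record kept by either diary or app. Ask app users to show or send their log to the leader each week. Have the leader note the mode used each week, and report mode by arm beside the adherence comparison.

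The rule should be in place before sessions start, because app logs that were never submitted may not be recoverable. The cost is a change of wording, one extra field in the leader's weekly log and a small task for app users. The drawback is that a week of app records is not fully equivalent to a week of paper diary, which is why mode should be reported and not just pooled.

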#### Perceived impact of intervention

A measure will be created for the study to assess participants’ perceptions of the effects of the training on their attitudes and behaviors. Items will include free response questions and forced-choice items and will be completed at the 6 month assessment.

##### Quality control and safety procedures

Intervention manuals specific to each condition will be developed. All group sessions will be audiotaped. To assess treatment fidelity, approximately 20% of sessions will be reviewed by study investigators to: 1) determine whether they can identify which condition the particular session belongs to, 2) assess whether key elements in each session are covered, and 3) whether any cross-contamination occurred. A data safety monitoring board (DSMB) will be established to assure safety and study integrity. Two faculty members with expertise in health behavior change and biostatistics will meet every 6 months to review progress and adverse events. They will make recommendations to the PI and report any concerns to the Institutional Review Board or Office of Research Administration.

##### Procedures to retain the sample

Retention at follow-up visits will be promoted through strategies used effectively in other studies (e.g., collecting contact information of relatives and friends who can be contacted if unable to reach the participant). For each data collection visit, participants will be scheduled by phone or email, sent reminders via mail/text/or email, and called/texted/or emailed the day before. Missed visits will be rescheduled. Childcare and costs for transportation will be provided to participants if these are significant barriers to assessment visits. If necessary, assessments will be completed at participants’ homes, workplaces, or an agreed upon public location. Participants may also be offered the option of completing assessments by phone or online. Participants will be given an honorarium of $10 at 3 months, $25 at 6 months, and $40 at 12 months for completing assessments. We expect completion rates ~90% at follow-up.

### Statistical analysis

#### Sample size, power and effect size

We will have 80% power for a two-tailed test at alpha = .05 to detect an effect size equal to d = .71 at the dyad level, and .62 at the individual level (adjusting for interdependence within dyads) [63] for our primary weight loss comparison. Although our statistical power is limited, we will be able to calculate the 95% confidence interval around the point estimate of the SDT-WL intervention effect that will allow us to conduct an accurate power analysis for a future efficacy trial.

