**Methods:**

Project TEAMS (Talking about Eating, Activity, and Mutual Support) is a randomized controlled trial testing a couples-based intervention, grounded in SDT, designed to change the social context of weight loss by training spouses to provide needs support for each other’s eating and physical activity behavior. Sixty-four couples will be randomized to either 6 months of behavioral weight loss treatment informed by SDT (SDT-WL) or to 6 months of standard behavioral weight loss treatment (BWL). Couples will attend weekly sessions for 6 months and will be assessed at 0, 3, 6, and 12 months. By bolstering needs support, SDT-WL is predicted to increase autonomous self-regulation and perceived competence and produce greater weight loss and maintenance than standard behavioral treatment. Exploratory analyses will examine the SDT process model prediction that the influence of needs support on treatment outcomes will be mediated by autonomous self-regulation and perceived competence.

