### Study aims

The primary aim of this study is to examine the impact of a couples weight loss program rooted in SDT on weight loss outcomes and needs support, autonomous self-regulation, and competence for behavior change. This enhanced needs support condition (SDT-WL) will be compared to a more traditional model of spouse involvement (i.e., spouses attend groups but receive no training in providing autonomy support; BWL). Couples (*n* = 64) will be randomized to 6 months of either SDT-WL or BWL and will be assessed at 0, 3, 6, and 12 months.

The primary hypotheses are that compared to BWL, SDT-WL will result in: 1) greater increases in needs support from spouses, 2) greater increases in autonomous self-regulation and competence for healthy behaviors, and 3) greater weight loss at 6 and 12 months. Secondary aims will compare SDT-WL and BWL on maintenance of weight loss (6–12 months), treatment adherence, and treatment satisfaction. Exploratory analyses will compare the influence of needs support on weight loss with more directive forms of support as well as examine whether the effect of needs support on weight loss is mediated by autonomous self-regulation and perceived competence as predicted by SDT.

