##### Recruitment, screening, and randomization

Couples will be recruited through advertisements in the local media and screened by phone for preliminary eligibility. If eligible, couples will be invited to an in-person orientation where detailed information about the study will be provided and informed consent obtained. Once baseline assessments are completed, eligible couples will be randomized via a simple, variable-block length randomization, which ensures fairly equal allocations and will make it difficult to guess future assignments.

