#### Statistical analyses to support the primary aims

Structural regression models that treat couple members as nested within dyads will be used to examine primary aims of the study [63] using the R package lavaan [64]. To analyze the primary hypothesis that SDT-WL versus BWL will achieve greater increases in perceived needs support from baseline to 6 and 12 months, needs support at each time point will be used as an outcome variable, controlling for baseline needs support. Full information maximum likelihood estimation (FIML) will be used to account for missing data. Any relevant between- and within-dyad covariates based on the preliminary analyses described above will also be included in the analysis. Dyadic analysis will examine primary hypotheses that SDT-WL versus BWL will display greater autonomous self-regulation and competence for healthy behaviors (i.e., eating and physical activity) and greater weight loss at 6 and 12 months using the same strategy outlined above.

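### The stated 80% power at d = .71 (dyad level) holds only if all 64 couples provide outcomes; it makes no allowance for the roughly 90% completion that the protocol expects

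*Protocol article*

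**What the plan says.** The sample size section of the protocol article claims "80% power for a two-tailed test at alpha = .05 to detect an effect size equal to d = .71 at the dyad level", and gives a second value, ."62 at the individual level (adjusting for interdependence within dyads"). Both are for the primary weight loss comparison, which the study aims place at 6 and 12 months. The section names no number of analysed couples, no attrition allowance and no within-couple correlation. It does concede in general terms that power is limited.

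On numbers, the abstract says "Sixty-four couples will be randomized to either 6 months of behavioral weight loss treatment informed by SDT (SDT-WL") or to the standard programme. The randomization section describes "simple, variable-block length randomization, which ensures fairly equal allocations". No increase in enrolment to cover dropout is described.

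On retention, the section on retaining the sample says "We expect completion rates ~90% at follow-up". It does not say whether this counts couples or individuals.

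On missing data, the section on the primary aims says "Full information maximum likelihood estimation (FIML) will be used to account for missing data".

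**The concern.** A power statement for a follow-up outcome should rest on the number expected to supply that outcome. Here the retention paragraph and the power paragraph stand next to each other, and the second does not use the first. If .71 already needs every randomized couple, the trial will have less than 80% power at .71 under its own retention forecast.

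What is at stake is interpretation. If the trial finds no difference, readers will take .71 and .62 as the effects it was equipped to detect, and both may be somewhat too small. No design decision turns on this.

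**Working it through.** **Inputs from the protocol article.** 64 couples (abstract, study aims, eligibility); two-sided alpha .05, 80% power, d = .71 at the dyad level and .62 at the individual level (sample size section); completion about 90% (retention section).

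**Assumptions.** Equal allocation, n = 32 couples per arm, read from the description of fairly equal allocations. A within-couple correlation ρ, which is not stated and is varied below.

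**1. Reproducing .71.** Compare couple means by a two-sample t-test with noncentrality d × √(n/2) and 2n − 2 degrees of freedom.
- n = 32: noncentrality at d = .71 is .71 × √16 = 2.84, with 62 degrees of freedom. Power is 79.8%, and d for 80% power is .711.
- The normal approximation gives 81.1% power at d = .71 and a detectable d of .700.

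The stated .71 is therefore the full-sample figure.

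**2. 90% completion, couples lost together.** 64 × .90 = 57.6 couples, or 28.8 per arm.
- Noncentrality at d = .71 is .71 × √14.4 = 2.69. Power is 75.4% (76.9% by the normal approximation).
- Detectable d at 80% power is .751 (.749 with 29 per arm; .738 by the normal approximation at 28.8).

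**3. 90% completion, individuals lost independently.** Both spouses are observed in .90² = .81 of couples and exactly one in 2 × .90 × .10 = .18. A complete couple carries information 2/(1 + ρ) and a single spouse carries 1, so the information retained relative to full data is

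.81 + .18 × (1 + ρ)/2.

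| ρ (assumed) | information retained | effective couples per arm | detectable d | power at .71 |
|---|---|---|---|---|
| .30 | .927 | 29.7 | .74 | 76.7% |
| .50 | .945 | 30.2 | .73 | 77.5% |
| .52 | .947 | 30.3 | .73 | 77.6% |

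By the normal approximation, power at ρ = .52 is 78.9%.

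**4. The individual-level figure.** On the individual scale, d(individual) = d(dyad) × √((1 + ρ)/2).
- If .62 also uses all 64 couples, the implied correlation is ρ = 2 × (.62/.711)² − 1 ≈ .52.
- With that ρ, couples lost together: .751 × √(1.52/2) = .655.
- With that ρ, individuals lost independently: .62/√.947 = .637.
- If .62 instead used 57.6 couples, the implied correlation would be 2 × (.62/.751)² − 1 ≈ .36, which is also possible.

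So .62 alone does not show which number of couples was used. If it was 64, loss of 10% of couples raises the detectable value by .751/.711 = 1.056, about 5 to 6%, whatever ρ is.

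**The case against.** **The two passages do not contradict each other.** This stands. The power section gives no analysed number and the retention section makes no power claim. A reader might infer a contradiction, but the documents support only that a full-sample figure was not adjusted for the expected loss.

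**Whole-couple loss is the least favourable reading.** This stands in part. The retention section speaks of participants, and the planned model nests individuals within dyads, so a couple with one observed spouse still contributes. On that reading the shortfall is about .02 in d and roughly 1 to 2.5 power points. It is smaller but still there, so the result is a range and not the single value .75.

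**The .62 is not shown to be wrong.** This stands. It would be tempting to say that it carries the same error. The same sentence gives both figures, so a common number of couples is the natural reading, but step 4 shows that a correlation near .36 with 57.6 couples would also yield .62.

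**The planned analysis is not an unadjusted t-test.** The models for the primary aims control for baseline and may include further covariates. If covariates explained about 10% of outcome variance (a correlation of about √.10 = .32), the gain would offset a 10% loss. The sample size section claims no such gain, however, and the unadjusted comparison at full enrolment already reproduces .71. The argument does not validate the stated figure. It does mean that the true power of the adjusted analysis cannot be determined from the article.

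**FIML handles the missing data.** It keeps incomplete couples in the likelihood and can limit bias, but it does not supply follow-up weights that were never observed. The benefit of one observed spouse is already counted in step 3.

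**Limited power is already admitted.** The article adds that the confidence interval will inform a future trial. This lowers the importance of the point, but a general caveat does not correct a specific number.

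**Conclusion.** The point holds for the dyad-level figure. The .71 is the 80% power value for 32 couples per arm with complete outcomes, and the protocol's own completion forecast is not carried into it. At about 90% completion the detectable d is about .75 if couples leave together and about .73 if individuals leave independently with a within-couple correlation near .5. Power at .71 is about 75% and 78% respectively. These results assume equal allocation and an unadjusted comparison of couple means, which is the calculation that reproduces the stated figure.

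The individual-level .62 probably moves to about .64 to .66, on the unproven assumption that it uses the same 64 couples. The point is minor: the shift is small, the article already concedes limited power, and the design is unaffected.

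**What to change.** Restate the sample size section so that the detectable effects refer to the expected number of completers. At the dyad level this means d of about .73 to .75 for 80% power with 64 couples randomized and about 90% completion, saying whether completion is counted by couple or by individual. Recompute the individual-level value on the same basis, using and stating the within-couple correlation that the sponsor itself assumed. The value of about .52 derived above is a back-calculation and should not be adopted as the planning assumption.

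The cost is a sentence or two and a slightly less favourable stated figure. No additional couples and no change to the design or analysis are required.
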